## **6. Study medication**

### **6.1 Investigational drug**

EPO besides promoting red cell formation has been shown to be protective against hypoxic-ischaemic and inflammatory injuries in a broad range of tissues and organs. Especially a protective effect on brain, retina and bowel could be shown in animal models and first human studies. Several mechanisms explaining this activity have been recognized: EPO inhibits glutamate release in the brain, modulates intracellular calcium metabolism, induces the generation of anti-apoptotic factors, reduces inflammation, decreases nitric oxide-mediated injury, and has direct antioxidant effects.

Very preterm infants may suffer from a variety of short-term complications and long-term sequelae of premature birth. The most critical period are the first days after birth and inflammatory changes as consequence of hypoxia-ischaemia or infection seems to have a major impact on short-term as well as permanent damage.

Because EPO have been shown to influence several mechanisms associated with these short-term and long-term complications of prematurity and furthermore has been shown to have a positive effect even post hoc, i.e. if given within a period of hours after an hypoxic-ischaemic insult, EPO may ameliorate the damage in very premature infants.

EPO has been used widely for several weeks in preterm infants to prevent anemia and is well tolerated. No short and long term adverse effects have been documented with EPO treatment in preterm infants.

Endogenous EPO production may contaminate the difference between EPO and placebo. However measured serum concentrations in non-newborn infants are 100 times lower than those expected after intravenous administration of 25 µg per kg. Some center give EPO routinely in anemic infants to reduce the need for blood transfusion. This low dose treatment is at the discretion of the physician after day 7 as it has been shown not to affect neurodevelopmental outcome.

### **Blinding, Packaging, Storage Instructions, Labelling, Shelf Life**

EPO or an equivalent volume of normal saline (NaCl 0,9%) placebo will be administered intravenously before 3 hours, at 12-18 and at 36-42 hours after birth. A single dose consists of 25 µg (3000 IU) human erythropoietin per kilogram body weight dissolved in 1 ml aqua dest. 1 ml per kilogram birth weight (not the actual weight) will be given intravenously within 3 minutes. The maximal dose is 37.5 µg (4500 IU) for infants weighing 1.5 kilograms or more. The packaging, blinding, labelling and storage of the medicine at the pharmacy conforms to the HMG, according to a randomisation list that is only known to the pharmacy.

The individual vials will be allocated unequivocally by their labelling (centre, patient number). Upon request, 1 container per patient will be supplied, allowing 3 days of treatment. Adequate refrigeration (+2 to + 8°C) must be provided during storage at the individual centres, as well as during shipment to the centres. The filled containers have a shelf life of at least 1 week in unopened condition, and are microbiologically innocuous. Unused samples must be stored by the individual centres until the end of the study, and then discarded at the centre in accordance with the monitors' instructions. Disposal of samples must be documented in a disposal protocol (included in the investigator's file).

### **Undesirable effects**

Serious, life-threatening side effects have not been observed to date, neither within the scope of approved application of Epo in adults, nor within the established therapy in preterm infants to prevent anaemia.

During and at least 24 hours after injection heart rate, arterial saturation (pulse oximetry) or transcutaneous pO2 and (arterial) blood pressure will be monitored and the infant will be observed clinically.

Haematological examination including haematocrit, haemoglobin, red and white cell count and thrombocytes will be done at day 7 to 10.

### **Description of Verum Treatment**

Recombinant human EPO is administered once daily. A single dose consists of 25 µg (3000 IU) human erythropoietin per kilogram body weight dissolved in 1 ml aqua dest. 1 ml per kilogram birth weight (not the actual weight) will be given intravenously within 3 minutes. The maximal dose is 37.5 µg (4500 IU) for infants weighing 1.5 kilograms or more.

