| Exclusion Criteria          | 
 
1. Genetically defined syndrome
 
2. Severe congenital malformation adversely affecting life expectancy
 
3. Severe congenital malformation adversely affecting neurodevelopment
 
4. A priori palliative care
 
5. Intracranial haemorrhage grade 2 or more
 
                                                                                                                                                                                                                                                                                  |
| Investigational drug        | Human erythropoietin, intravenous application Dosage: 3000 U/kg of body weight, Administered three times, at 3 hours, 12 to 18 hours and 36 to 42 hours after birth.                                                                                                                                                                                                                                                                                                                                                                                                                                                        |
| Comparison therapy          | NaCl 0.9%, same administration route and volume as investigational drug                                                                                                                                                                                                                                                                                                                                                                                                                                                                                                                                                     |

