## 2.2.2 Pharmacokinetics of EPO

Studies in rats and sheep have shown greater clearances, shorter half-lives, shorter residence times and greater distribution volumes after i.v. bolus of EPO in fetuses and newborns compared to adults. Consequently the recommended dose per kg body weight for prevention of anaemia is higher in preterm infants than in adults.

Single dose pharmacokinetics of EPO have been studied in preterm infants after intravenous and subcutaneous administration. Mean ( $\pm$ SD) volume of distribution was 300 ( $\pm$ 72) ml/kg, total body clearance 27 ( $\pm$ 9) ml/h\*kg, half life 8 ( $\pm$ 3) hours and maximum serum concentration 711 ( $\pm$ 166) U/l after 200 U/kg i.v. In the stroke trial serum levels rose to 5649 ( $\pm$ 903) mU/ml after the third dose of 33'000 U i.v. resulting in cerebrospinal fluid concentrations of 17.1 ( $\pm$ 5.6) mU/ml which is 60 to 100 times that of non-treated patients.

To be neuroprotective EPO must cross the blood-brain barrier. This has been shown to occur in rats after experimental brain injury and in sheep and nonhuman primates. Juul et al showed a huge increase of endogenous EPO after asphyxia in the cerebrospinal fluid in human newborns (225 $\pm$ 155 mU/ml, range 7 to 2350 mU/ml) compared to control infants (6 $\pm$ 1 mU/ml).

The minimal effective dose for neuroprotection in preterm infants is not known. In the adult stroke trial 100'000 IU EPO divided in three doses were given intravenously and were safe and effective. In rats 5'000 U/kg had the same effect as 10'000 U/kg, both were well tolerated (REF Wang 2004). We consider a dose of 3'000 U/kg as sufficient to achieve a CSF concentration of 5U/ml assuming a Serum/CSF ratio of 100 to 1000.

Recently new derivatives of EPO have been engineered. Darbepoetin- $\alpha$  has 3-fold longer half-life than epoetin- $\alpha$ . Carbamylated EPO and asialerythropoietin are tissue protective but not erythropoietic. These substances are not yet established in clinical routine and their specific properties, e.g. longer survival and lack of erythropoietic effect, have no advantage over the classical EPO in preterm infants.

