### **6.5 Description of Placebo Treatment**

NaCl 0,9% is administered once daily. A single dose consists of 1 ml NaCl 0,9% per kilogram body weight. 1 ml per kilogram birth weight (not the actual weight) will be given intravenously within 3 minutes.

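### The dosing sections disagree on schedule (once daily versus three doses by 42 h) and on placebo volume above 1.5 kg, and the CSF figure in the dose rationale does not follow from its own pharmacokinetics

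*Protocol*

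**What the plan says.** **Schedule.** The Protocol Synopsis describes the drug as "Administered three times, at 3 hours, 12 to 18 hours and 36 to 42 hours after birth". Section 6.2 agrees apart from the first dose: "EPO or an equivalent volume of normal saline (NaCl 0,9%) placebo will be administered intravenously before 3 hours, at 12-18 and at 36-42 hours". The research plan in 2.1 gives the same three time points, the diagram in 1.7 shows three doses, and the time table in 1.6 marks three administrations on days 1-3. Section 6.4, which defines the verum treatment, says instead "Recombinant human EPO is administered once daily", and section 6.5 says "NaCl 0,9% is administered once daily". Neither 6.4 nor 6.5 gives a number of doses or time points.

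**Volume.** Sections 6.2 and 6.4 dissolve 3000 IU per kg in 1 ml, dose by birth weight at 1 ml/kg, and add a cap: "The maximal dose is 37.5 µg (4500 IU) for infants weighing 1.5 kilograms or more". Section 6.5 says of placebo "A single dose consists of 1 ml NaCl 0,9% per kilogram body weight", again by birth weight, with no cap. The synopsis requires placebo to match the drug in route and volume, and 6.2 also requires equivalent volumes. The synopsis and the research plan give 3000 U/kg without a cap.

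**Dose rationale.** Section 2.2.2 reports, for preterm infants, a peak of 711 U/l after 200 U/kg i.v., a distribution volume of 300 ml/kg, a clearance of 27 ml/h per kg and a half-life of 8 h. It then calls 3000 U/kg "sufficient to achieve a CSF concentration of 5U/ml assuming a Serum/CSF ratio of 100 to 1000".

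**The concern.** Sections 6.4 and 6.5 are where a centre looks up how each treatment is given. If they differ from the synopsis and 6.2 on timing, two centres can each follow the protocol and give different schedules. If they differ from each other on volume, staff who do not know the arm have no single rule for an infant above 1.5 kg, and the masking described in 6.2 then rests on 6.5 not being applied as written.

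The CSF sentence is a separate matter. It supports the choice of dose with a concentration that should follow from figures given a few lines earlier, and it does not.

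**Working it through.** **1. Schedule.** Time points from the synopsis (3 h, 12-18 h, 36-42 h) and from 6.2 (before 3 h, then the same windows).

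- Shortest gap between doses 1 and 2: 12 - 3 = 9 h. Longest, with dose 1 at birth as 6.2 permits: 18 - 0 = 18 h.
- Gap between doses 2 and 3: 36 - 18 = 18 h to 42 - 12 = 30 h.
- Dose 2 is due by 18 h, so two doses always fall in the first 24 h of life, and all three are due by 42 h.

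**2. Volume.** The cap reproduces: 1.5 kg x 3000 IU/kg = 4500 IU and 1.5 kg x 25 µg/kg = 37.5 µg (120 IU/µg in both cases). At 3000 IU per ml it equals 4500 / 3000 = 1.5 ml.

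For a birth weight of 2.0 kg:

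| Source, read literally | Content | Volume |
|---|---|---|
| 6.4, verum | 4500 IU (4500 / 2.0 = 2250 IU/kg) | 1.5 ml |
| Synopsis and 2.1, verum, no cap stated | 2.0 x 3000 = 6000 IU | 2.0 ml at 3000 IU/ml |
| 6.5, placebo | saline | 2.0 ml |
| Synopsis and 6.2, placebo | saline | equal to verum |

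Placebo under 6.5 is 2.0 / 1.5 = 1.33 times verum under 6.4. Up to and including 1.5 kg the volumes agree.

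**3. CSF concentration.** The inputs of 2.2.2 agree with one another: 200 / 0.3 = 667 U/l against the reported 711 U/l, and ln 2 x 300 / 27 = 7.7 h against the reported 8 h.

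- Serum peak scaled by dose: 711 x (3000 / 200) = 10,665 U/l = 10.7 U/ml. From dose over volume: 3000 / 300 = 10 U/ml.
- CSF at a ratio of 100: 10.665 / 100 = 0.107 U/ml. At 1000: 10.665 / 1000 = 0.0107 U/ml.
- Stated over derived: 5 / 0.107 = 47 and 5 / 0.0107 = 469. With dose over volume: 50 and 500.

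Variants, at ratios of 100 and 1000:

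| Variant | Stated 5 U/ml over derived |
|---|---|
| Peak + 1 SD (877 U/l after 200 U/kg) | 38 and 380 |
| Peak - 1 SD (545 U/l after 200 U/kg) | 61 and 612 |
| Accumulation, half-life 8 h, most favourable timing | 32 and 321 |
| Accumulation, half-life 11 h (mean + 1 SD) | 30 and 299 |

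In the 8 h row the highest level follows dose 2, given 9 h after dose 1: 10.665 x (1 + 2^(-9/8)) = 10.665 x 1.459 = 15.6 U/ml in serum. No variant reaches 5 U/ml within the stated range of ratios. With the single-dose peak it would need a ratio of 10.665 / 5, about 2.

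**4. Comparison with the adult stroke trial in 2.2.2.** Its ratio is 5649 / 17.1 = 330. Applied here, CSF is 10,665 / 330 = 32 mU/ml, which is 155 times below 5 U/ml but 32.3 / 17.1 = 1.9 times that trial's own CSF level. The serum ratio is also 10.665 / 5.649 = 1.9.

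**The case against.** **Schedule.** The three time points stand in the synopsis, 2.1, 6.2 and the diagram, against one sentence each in 6.4 and 6.5, which may be leftover wording. Section 6.2 also speaks of a container for 3 days of treatment, and for an infant born late in the day the three windows can fall on three calendar dates. That makes actual divergence between centres less likely. It does not make the sections agree: an infant born in the early morning would have doses 1 and 2 on the same date.

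**Volume.** A reader might infer that the arms were meant to receive different volumes and that volume would reveal allocation. The documents do not support this. The synopsis and 6.2 require equal volumes, vials are labelled by centre and patient number, only the pharmacy holds the list, and nothing says that it fills by an arm-specific volume. Staff who do not know the arm cannot give arm-specific volumes either. What stands is that 6.5 omits a limit given in 6.2 and 6.4, and that masking is at risk only if 6.5 is applied as written.

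**CSF sentence.** It is background and feeds no endpoint, sample size or analysis in the protocol. The factor rests on a 15-fold extrapolation from 200 to 3000 U/kg under dose-proportional kinetics, which the protocol neither states nor tests. The printed unit may also be a slip: if 5 mU/ml was meant, the derived level exceeds it by 10.7 / 5 = 2.1 to 107 / 5 = 21 times. The documents do not settle which. All of this stands as a limit on the conclusion, but the sentence as printed is still not reproduced.

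**Conclusion.** The schedule and volume conflicts are in current operative text and must be reconciled. Sections 6.4 and 6.5 do not match a plan in which doses 1 and 2 are 9 to at most 18 h apart. Above 1.5 kg, 6.5 conflicts with the equal-volume requirement, by 0.5 ml at 2.0 kg. The protocol gives no birth-weight distribution, so the share of infants affected cannot be stated.

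The CSF figure fails on its own inputs. Under dose-proportional kinetics the single-dose peak is 0.01-0.11 U/ml, roughly 47-470 times below the stated 5 U/ml, or about 30-320 times with accumulation at the stated mean half-life of 8 h.

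A reader might go further and infer that the dose is inadequate, or that a null result could not be read as absence of effect. That does not follow. Section 2.2.2 says the minimal effective dose is not known and never argues that 5 U/ml is necessary. The derived levels are about 1.9 times those of the stroke trial that it calls effective, at that trial's own ratio. The finding is that one printed justification is numerically wrong.

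**What to change.** - Bring the synopsis, the research plan in 2.1, and sections 6.2, 6.4 and 6.5 to one schedule. Include the timing of the first dose, which the synopsis puts at 3 h and 6.2 before 3 h.
- State one rule from birth weight to volume in ml, with or without a limit, worded identically for verum and placebo so that it can be applied without knowing the arm.
- Check the pharmacy instructions against the reconciled text.
- Recompute the CSF sentence in 2.2.2 from the cited pharmacokinetics, confirm the unit, and state the assumptions (dose proportionality, single dose or accumulated, serum/CSF ratio).

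Which schedule, cap or dose applies is for the sponsor's clinicians. The cost is a text amendment and a check of the pharmacy instructions. The stated CSF concentration may become lower; no sample size or analysis changes.

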### **6.5 Description of Placebo Treatment**

NaCl 0,9% is administered once daily. A single dose consists of 1 ml NaCl 0,9% per kilogram body weight. 1 ml per kilogram birth weight (not the actual weight) will be given intravenously within 3 minutes.

## **Allowed/Disallowed Concomitant Medication**

Any concomitant medication that is medically indicated for a patient will be allowed within the study.

## **Reference Sample**

A reference sample will be stored by the pharmacy in line with the safety measures demanded until the end of the study.

## **7. Study Procedures and Examination Methods**

### **Inclusion in the Study, Beginning of Study**

All patients will be assessed with regard to inclusion/exclusion criteria (sections 5.2 and 5.3). If the criteria are met, the patient shall be included in the study after parental consent has been obtained, and treatment shall immediately be initiated.

The study medication will be obtained from the responsible pharmacy (cf. 6.2). It will be supplied on request. The study centres will be randomised separately.

### **7.2 Study-related Procedures**

Within the study, the following tests will be performed routinely (medically indicated tests and examinations):

1. Minimal electronic monitoring includes heart rate (or pulse rate) with recommended alarm limits at 90 and 180 beats per minute, arterial saturation (pulse oximetry) with recommended alarm limits at 85% and 95%.
2. Arterial blood pressure will be monitored continuously if there is an indwelling arterial line and intermittently by oscillometric measurement at least every 8 hours during the first 7 days.
3. In selected infants cerebral perfusion and oxygenation will be monitored with near infrared spectroscopy (NIRS) 10 min before until 60 minutes after first epo/placebo dose (optional).
4. Serial cerebral ultrasound assessment will be carried out on day 1 and 7 to 10 and then every 14 days until 360/7 weeks postmenstrual age (or at discharge if discharged before) to detect intracranial haemorrhage graded after Papile, ventricular dilatation and white matter disease (periventricular echodensities at 7 to 10 days and periventricular leukomalacia at 36 postmenstrual weeks). The final cerebral ultrasound includes the worst findings in that hospitalisation.
5. Both eyes are examined by an ophthalmologist to detect retinopathy of prematurity (ROP). The severity of ROP will be graded according to the international classification of ROP.
6. Necrotising enterocolitis is diagnosed by clinical signs (abdominal distension, bilious aspirates, and/or bloody stools) and either pneumatosis intestinalis, hepatobiliary gas, or free intraperitoneal air on abdominal x-ray or at laparotomy. Severity of enterocolitis will be graded according to presence and severity of complications.
7. Septicaemia is diagnosed by clear clinical, radiological, or histological evidence of infection and at least one microbiologically relevant positive blood culture.
8. Persistent ductus arteriosus (PDA) is diagnosed clinically or with echocardiography and documented only if drug treatment (indomethacin or ibuprofen) or surgical ligation is required.
9. Weight and head circumference are recorded at birth, at 7 to 10 days, at 360/7 postmenstrual weeks, at 24 months and 5 years corrected age.
10. Optional MRI examination of the head will be performed at the age of 40 (+/- 4 weeks) postmenstrual weeks. Data will be analysed by Prof. [name], Geneva.

### 7.3 Study-related Tests and Examinations

To determine whether early administration of EPO alters the incidence and severity of complications typically associated with preterm birth in infants born between 260/7 and 316/7 gestational weeks at birth. Specifically severity of intracranial haemorrhage with its sequelae, white matter disease (periventricular leukomalacia), retinopathy and necrotising enterocolitis and its complications will be monitored, respectively. Further complications such as bronchopulmonary dysplasia (oxygen dependency at 36 weeks postmenstrual age), septicemia and persistent ductus arteriosus (PDA) will be looked after as well.

Within the study, the following tests will be performed in addition to the medically indicated tests and examinations (cf. 10.2):

1. Placental histology will identify prenatal risks such as amnion infection and placental malfunction. Adaptation will be documented with the APGAR score at 1, 5 and 10 minutes.
2. A sample of umbilical cord serum will be stored to determine the concentration of endogenous EPO (Prof. [name], Berlin)
3. The Clinical Risk Index for Babies (CRIB). The CRIB is a simple tool for assessing neonatal risk based on the variables gestational age, birth weight, congenital malformations, lowest and highest appropriate FiO2 and worst base deficit within the first 12 hours of life.

### 7.4 Magnetic resonance imaging

In addition to the original protocol MRI imaging at 40 weeks gestation shall be used to quantify the effect of EPO on brain growth, specifically on the cerebral white matter (WM).

#### 7.4.1. Rationale for using MRI

Recent advances in **magnetic resonance (MR) techniques** show great potential to expand our understanding of brain development and brain injury in the living infant. Conventional T1 and T2 weighted imaging can show signal abnormality in the periventricular WM that are different from the cystic lesions detected by ultrasound. The typical conventional MR imaging pattern in the subacute phase consists of punctate periventricular areas of T1 signal hyperintensities and T2 signal hypointensities. In several recent studies on preterm infants brain diffuse excessive high signal intensity (DEHSI) in the cerebral WM on T2-weighted imaging was reported to be present in up to 40 to 75% of low birthweight preterm infants imaged at term.

The MR techniques provide a unique ability to measure the impact of EPO on subsequent brain development. Specifically, the development of 3D **volumetric MRI** techniques allows quantification of the absolute volume of cerebral WM, both myelinated and unmyelinated components, as well as cortical gray matter and basal structures such as the striatum.

With the advent of improved imaging techniques the hypothesis of a sensitive period of brain development in the last trimester of gestation becomes increasingly testable. To study effects of extrauterine life on brain development a group of healthy preterm infants (<32 weeks at birth) and a group of healthy fullterm infants underwent conventional MR-imaging at 40-41 weeks with semi-quantitative analysis. The preterm infants at term showed significantly less gray/WM differentiation and less myelination. They also showed poorer neurobehavioral performance.

## Volumetric 3D-MRI and Segmentation Image Processing: Acquisition of Normative Data in Preterm Infants

In a subsequent study the group developed advanced volumetric 3D-MRI techniques to focus on more detail of brain development in the period from 28 weeks to term and elaborate on the processes likely to underlie the preterm/fullterm differences found at term described in the earlier study. Post acquisition image processing with tissue segmentation algorithms were developed to quantitate total brain volume and absolute volumes of gray and WM in premature and term infants. While total brain tissue volume exclusive of cerebrospinal fluid (CSF) was found to increase in the period of 29 to 41 weeks, the principal determinant was found to be an increase in gray matter volume (GM) from 35 to 50% that related to a fourfold increase in cortical GM volume rather than in subcortical GM volume. This increase is thought to primarily relate to cortical differentiation rather than to an increase in the total number of neurons. The cortical GM volume increase was found to be associated with significant increase in surface area and gyral development. Furthermore we have been able to distinguish and quantitate the absolute volumes of both myelinated and unmyelinated WM (WM). Prior to 36 weeks of gestation, unmyelinated WM was the dominant type of brain tissue. However, starting at 35 weeks and up to 41 weeks an almost 5-fold increase in absolute volume of myelinated WM was observed. This MR technique gives us the ability to measure quantitatively the impact both on myelination and cortical development of insults at the critical period of brain development.

